**Figure 2 figure2:**
[figure not shown]
Study design. ATTR-CM: transthyretin amyloid cardiomyopathy; ICF: informed consent form. The “index date” marks the point of first diagnosis, which may coincide with or precede study enrollment. Patients are then followed over time, capturing both retrospective data (before the index date) and prospective data (after the index date), at approximately 3-month intervals. The “observation period” extends from the index date until either the end of the study, patient death, withdrawal of consent, or loss to follow-up. Data are collected through a combination of retrospective review during a one-time medical record abstraction and routine clinical visits for prospective information.

#### Study Participants

The inclusion criteria of this ATTR-CM registry are as follows: (1) adults (aged ≥18 years) at first ATTR-CM diagnosis; (2) confirmed diagnosis of ATTR-CM after June 1, 2019; and (3) able to provide informed consent. The eligibility criteria are broad enough to include all patients with ATTR-CM without any exclusion criteria.

Several strategies to address potential selection bias will be implemented. Each eligible patient will be consecutively assessed during the designated period using predefined criteria to ensure comprehensive inclusion and reduce bias. Recruitment will span a variety of clinical settings to capture a diverse and representative sample. The eligibility criteria are designed to be broad, promoting inclusivity and enhancing the generalizability of our findings. In addition, a screening log for individuals who do not participate will be maintained to gather minimal deidentified information to identify any systematic differences and further understand potential biases. Each enrolled participant or his or her legally acceptable representative will be provided with an informed consent form (ICF) that outlines the study objectives, procedures, risks, and benefits, and clearly states that participation is voluntary with the option to opt out at any time without affecting their clinical care.

#### Data Collection and Management

All variables described below will be collected as part of routine clinical practice or following standard practice guidelines in the countries where this study is being conducted. This study will not provide or recommend any treatment; all decisions regarding treatment will be made at the sole discretion of the treating physician, in accordance with their routine clinical practice administration of any specific assessment tools is not mandated and all clinical decisions will be made solely at the discretion of the treating physician in accordance with the local and international guidelines. The data to be collected retrospectively at enrollment and prospectively during follow-up is listed in Textbox 2.

Data to be collected retrospectively at enrollment and prospectively during follow-up.Demographic data (age at enrolment, sex, and race or ethnicity).Diagnosis of transthyretin amyloid cardiomyopathy (ATTR-CM; date of first ATTR-CM diagnosis, age at first ATTR-CM diagnosis, method of diagnosis, etc).Physical measurements (height, weight, smoking status, blood pressure, and heart rate).Relevant medical history and comorbidities (first clinical cardiac symptom related to ATTR-CM, symptom onset date as the date of the first clinical symptom attributed to ATTR-CM, age at onset of symptom, treatment received for the first symptom if applicable with its start and stop dates).Emergency department visits.Type of ATTR-CM (wild-type ATTR or hereditary ATTR [hATTR] with genetic variants identified if applicable for patients with hATTR).Family history (known cardiomyopathy, polyneuropathy, and sudden cardiac death [among parents, siblings, and second- or third-degree family links]).Treatment for ATTR-CM (ATTR-specific pharmacologic treatment, including, treatment name, dosage, prescribed frequency, start date, end date, and any change in treatment).Prescription of heart and cardiovascular medication (including beta-blockers, angiotensin-converting enzyme inhibitors, angiotensin receptor-neprilysin inhibitors, angiotensin II receptor blockers, digoxin, calcium channel blockers, diuretics, antiplatelets, lipid-lowering agents, and anticoagulants (within 6 months before the index date).Concomitant medications (including heart and cardiovascular medications and other concomitant medications from the index date).New York Heart Association functional class (closest available measurement to the index date).Kansas City Cardiomyopathy Questionnaire.Imaging and lab assessments (date of assessment and results).Survival status (date of death, reason for death: Cardiovascular-related, not cardiovascular-related, and indeterminate).Hospitalization (date of admission, date of discharge, reason for hospitalization categorized as cardiovascular-related, not cardiovascular-related, and indeterminate).Adverse events with explicit attribution to any of the study sponsor’s drugs.

Multimedia Appendix 1 provides further details on each data collection element, including the timepoints at which the data will be recorded. The study case report form (CRF) includes an “ATTR-CM diagnosis” section detailing the methods used to diagnose ATTR-CM. The CRF captures a range of clinically validated approaches, including functional classification, imaging, biomarker screening, and genetic testing, consistent with established guidelines for ATTR-CM diagnosis.

The collected data will be from reliable sources of patient-level information available at the participating sites. This includes data available in the patients’ electronic medical records as well as medical charts and any other documentation or communication by health care providers. All data listed above will be collected by trained site personnel and entered directly into the web-based electronic case report forms (eCRFs) at each participating study site. Sites will be responsible for entering extracted patient data into a secure Electronic Data Capture (EDC) database and all changes or corrections to eCRFs will be documented in an audit trail. The personal data will be stored at the study site in encrypted electronic or paper form and will be password-protected or secured in a locked room to ensure that only authorized study staff have access. Patient data will be deidentified before analysis. All identifiable information will be replaced with a unique patient-specific identifier, and data will be transmitted and managed using encryption.

### Data Analysis

Detailed methodology for summary and statistical analyses of data collected in this study is documented in a statistical analysis plan. This study is descriptive and does not involve hypothesis testing, hence the actual sample size will be determined by the number of eligible ATTR-CM cases identified in the medical records that meet the inclusion criteria. Approximately 350 patients diagnosed with ATTR-CM are expected to be enrolled based on feasibility assessments, historical diagnosis rates, and the expected patient volume at the 17 participating sites across Taiwan, Hong Kong, and Malaysia. Continuous variables will be summarized using descriptive statistics, including the number of participants with nonmissing and missing values, mean, SD, median, 25th percentile (Q1), 75th percentile (Q3), minimum, maximum, and median (IQR). Means and medians will be presented with one more decimal place than the raw data, while SDs will be presented with 2 more decimal places. Categorical variables will be summarized using frequency counts (n) and percentages (%), with percentages calculated over nonmissing data.

Time-to-event analysis will be performed using the Kaplan-Meier methodology. Data will be presented as the number of patients at risk, with the event, and censored. The estimated median, Q1, Q3, and the 2-sided 95% CI, using Brookmeyer and Crowley method, will be provided for the main statistical estimators. CIs about a parameter estimate will be presented using the same number of decimal places as the parameter estimate.

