### Aims and Objectives

This study aims to understand the natural history and treatment patterns of patients with ATTR-CM in Taiwan, Hong Kong, and Malaysia. Primary, secondary, and exploratory objectives, respectively, are listed in Textbox 1.

Study objectives.To characterize the natural history of patients with transthyretin amyloid cardiomyopathy (ATTR-CM), described by patient demographic and clinical characteristics at diagnosis of patients with ATTR-CM, and patient outcomes.To describe the treatment patterns in patients with ATTR-CM and to identify the prognostic factors for all-cause mortality and cardiovascular-related hospitalization in patients with ATTR-CM.To assess treatment effectiveness in patients with ATTR-CM and to evaluate the quality of life and health care resource usage in patients with ATTR-CM.

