## Methods

### Study Design and Setting

This multicenter, noninterventional, disease registry enrolling approximately 350 patients diagnosed with ATTR-CM will be conducted across approximately 17 sites in Taiwan, Hong Kong, and Malaysia. All patients with a documented diagnosis of ATTR‑CM after June 1, 2019 will be invited to participate in the study. The study size will be based on the number of eligible ATTR-CM cases identified in the medical records and meeting the inclusion criteria. However, the goal is to enroll approximately 350 patients diagnosed with ATTR-CM across the sites, with data collected throughout routine clinical practice. As it is a noninterventional study, no procedures or treatments will be mandated, and patients will receive their usual clinical care. The observation period for each patient will range from the index date (ie, the date of first documented ATTR-CM diagnosis) to whichever occurs first of death, patient withdrawal of consent, loss to follow-up, or end of data collection. The end of data collection is planned for a minimum of 12 months after the end of the enrolment period. This will allow all patients to have the opportunity to contribute at least 12 months of follow-up data (Figure 2).

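### Kaplan-Meier is named without exception; applied to cardiovascular hospitalization alone, it would censor deaths and overstate the proportion hospitalized

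*Protocol article*

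**What the plan says.** The Data Analysis section gives one general rule: time-to-event "analysis will be performed using the Kaplan-Meier methodology". It then sets the form of the output. "Data will be presented as the number of patients at risk, with the event, and censored". The summaries are also set: "The estimated median, Q1, Q3, and the 2-sided 95% CI, using Brookmeyer and Crowley method, will be provided for the main statistical estimators". No endpoint is listed for these analyses, no competing-event category appears, and no other time-to-event method is named in the article. The section leaves detailed methodology to a statistical analysis plan (SAP), which is not shown.

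Three other places bear on the point:

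- **Aims and Objectives** includes the aim to "identify the prognostic factors for all-cause mortality and cardiovascular-related hospitalization in patients with ATTR-CM". Hospitalization therefore stands beside mortality as a separate outcome.
- **Study Design and Setting** follows each patient from first documented diagnosis to "whichever occurs first of death, patient withdrawal of consent, loss to follow-up, or end of data collection".
- **Data Collection and Management** (Textbox 2) records admission and discharge dates with the reason for hospitalization, the date of death, and "reason for death: Cardiovascular-related, not cardiovascular-related, and indeterminate".

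**The concern.** A patient who dies without a cardiovascular admission can never have one. Kaplan-Meier with death censored treats that patient as still at risk and as having the same future hospitalization risk as the survivors. The curve then estimates risk in a hypothetical population in which nobody dies, and 1-KM is not the proportion of patients hospitalized.

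Deaths will not be rare here. The Introduction describes the disease as fatal when untreated, and the Abstract says that deceased patients are enrolled by record review. The study is presented as descriptive, so a reader would take a hospitalization curve and its quartiles as a description of what happens to these patients. The required quartiles add a second problem: Kaplan-Meier can return an upper quartile that the real population never reaches.

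**Working it through.** The article gives no hospitalization rate, mortality rate or event count, so it has no figure to reproduce. All rates below are assumptions, used to show direction and size.

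**Inputs**

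- *h*: hazard of first cardiovascular hospitalization, assumed constant, 0.2 to 0.4 per year.
- *m*: hazard of death without prior cardiovascular hospitalization, assumed constant, 0.05 to 0.25 per year.
- Longest possible follow-up: diagnosis after June 1, 2019 (Study Participants) to end of data collection on October 1, 2027 (Results), about 8.3 years. Horizons of 3 and 5 years are therefore within reach for the earlier diagnoses. The follow-up opportunity intended for every patient is at least 12 months (Study Design and Setting).

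**Formulas**

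- With death censored: 1-KM(t) = 1 − exp(−h·t)
- Actual proportion hospitalized: CIF(t) = h/(h+m) × [1 − exp(−(h+m)·t)]

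The two are equal only if m = 0. For any m above 0, 1-KM is the larger.

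**Results at 3 years**

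| h | m | 1-KM | CIF | Excess (points) |
|---|---|---|---|---|
| 0.2 | 0.05 | 45.1% | 42.2% | 2.9 |
| 0.3 | 0.15 | 59.3% | 49.4% | 10.0 |
| 0.3 | 0.20 | 59.3% | 46.6% | 12.7 |
| 0.4 | 0.25 | 69.9% | 52.8% | 17.1 |

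The excess is taken before rounding.

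One row in full, h = 0.3 and m = 0.15: 1 − exp(−0.9) = 0.593; (0.3/0.45) × [1 − exp(−1.35)] = 0.667 × 0.741 = 0.494.

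**Range by horizon over the whole grid**

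- 1 year: 0.4 to 3.6 points.
- 3 years: 2.9 to 17.1 points.
- 5 years: 6.1 to 27.3 points.

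**Quartiles, h = 0.3 and m = 0.15**

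- First quartile: Kaplan-Meier −ln(0.75)/0.3 = 0.96 years; cumulative incidence −ln(1 − 0.25/0.667)/0.45 = 1.04 years.
- Median: Kaplan-Meier ln 2/0.3 = 2.31 years; cumulative incidence −ln(1 − 0.5/0.667)/0.45 = 3.08 years.
- Third quartile: Kaplan-Meier ln 4/0.3 = 4.62 years. The cumulative incidence never passes 0.3/0.45 = 67%, so no third quartile exists.

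**Simulation check.** The formulas were tested on 200,000 simulated patients, with censoring uniform between 1 and 8.33 years and annual cause-specific risks of 30% (hospitalization) and 15% (death). At 3 years the simulation gave 65.9% against 54.4%. The formulas give 65.7% against 54.2%.

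**The case against.** The strongest reply is that the article never states the analysis being criticised. The Kaplan-Meier sentence lists no endpoints and does not mention hospitalization. Death as an end of observation defines follow-up; it is not expressly a censoring rule for a non-fatal endpoint. All-cause mortality, or a composite of death and hospitalization, would fit the sentence and carry no such bias. The named objective concerns prognostic factors, and cause-specific hazard regression that censors death is a valid way to study them. Detail by endpoint may be in the SAP.

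Most of this stands, and it makes the point conditional. It does not remove the point. The article sets a method and an output scheme without exception, and that scheme gives a patient who dies first no place except among the censored. An SAP that used cumulative incidence would depart from this wording. A valid regression for prognostic factors also does not turn 1-KM or its quartiles into a valid description of risk.

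A reader might infer more than the document supports:

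- **That hospitalization risk will be overstated.** This follows only if hospitalization is analysed alone, with death censored and 1-KM read as actual risk.
- **That cumulative hospitalization risk is a stated outcome.** Hospitalization is named only in the prognostic-factor objective and as a data item.
- **That cardiovascular death will be shown by Kaplan-Meier.** Cause of death is recorded, but no such curve is planned in the text; the mortality named in the objectives is all-cause.
- **That comparisons by ATTR type or country will be distorted.** The analysis section plans no such time-to-event comparisons. Cross-country comparison appears in the Introduction as motivation.

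**Conclusion.** The point holds in conditional form. If first cardiovascular hospitalization is analysed alone under the stated rule, the proportion hospitalized would be overstated and the median and quartiles would be too early. The direction is certain wherever deaths occur before hospitalization.

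The size rests entirely on assumed constant hazards. Over the range used, the overstatement is small at 1 year and about 3 to 17 points at 3 years. Describing the disease as fatal when untreated does not supply a mortality rate for a registry that also records treated patients, so no single value in that range can be claimed. All-cause mortality and composites that include death are unaffected. The change should be made, but the problem does not undermine the registry.

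**What to change.** In the Data Analysis section, and in the SAP if it follows the same rule:

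- Limit Kaplan-Meier and Brookmeyer-Crowley quantiles to all-cause mortality and any composite that includes death.
- For first cardiovascular hospitalization, report the Aalen-Johansen cumulative incidence with death as a competing event, with 95% CIs at fixed time points.
- If cardiovascular death is analysed separately, treat it the same way, with other-cause death competing.
- Add a competing-event count to the at-risk, event and censored display.
- Cause-specific hazard regression that censors death can stay for the prognostic-factor objective.

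The cost is a sentence or so of text and standard software. The admission dates, death dates and causes needed are already collected. The final report is not due until June 1, 2028. The downside is that a median time to hospitalization may not be reportable where fewer than half of the patients are ever hospitalized.

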In Hong Kong, ethics approvals have been obtained from the Hospital Authority’s Central IRB for Queen Elizabeth Hospital and Princess Margaret Hospital (date of approval September 25, 2024, Central IRB reference number CIRB-2024-334-5), the Joint Chinese University of Hong Kong–New Territories East Cluster Clinical Research Ethics Committee (CREC) for Prince of Wales Hospital (date of approval: September 15, 2024, CREC reference number 2024.351) and by the IRB of the University of Hong Kong Hospital Authority Hong Kong West Cluster for Queen Mary Hospital (date of approval January 8, 2025, IRB reference number UW 24-623). An ethics application is being prepared for submission to the Hospital Authority Central IRB for Tuen Mun Hospital. In Malaysia, approvals have been obtained from the Medical Research Ethics Committee of Hospital Sultan Idris Shah in Serdang and the Sarawak Heart Centre (date of approval November 8, 2024, number 24-02846-UQ8). The application is currently under review by the IRB of the Medical Research Ethics Committee of Institut Jantung Negara Sdn Bhd.

Each enrolled participant or his or her legally acceptable representative will be provided with an ICF that outlines the study objectives, procedures, risks, and benefits, and clearly states that participation is voluntary with the option to opt out at any time without affecting their clinical care. No compensation will be provided to study participants.

## Results

The study began on October 1, 2024, with the first participant’s visit, and as of March 16, 2025, a total of 59 patients have been recruited. These include 35 patients enrolled from National Taiwan University Hospital, 13 patients recruited from Taipei Veterans General Hospital, and 2 patients enrolled from China Medical University Hospital in Taiwan. Two patients have been recruited from Sarawak Heart Center in Malaysia, and 7 patients enrolled from Queen Mary Hospital in Hong Kong. We anticipate that data collection will continue robustly, with an interim report scheduled for completion by December 31, 2025. The final phase of data collection, marked by the last participant’s visit, is planned for October 1, 2027, and the final study report is expected to be finalized by June 1, 2028. Once established, the resulting database will serve as a valuable resource for analyzing baseline characteristics, treatment patterns, and outcomes in patients with ATTR-CM. This extensive dataset will not only provide insights into current clinical management but also guide future research efforts and inform evidence-based clinical practices in managing ATTR-CM.

## Discussion

### Anticipated Findings

The aim of this study is to understand the natural history and treatment patterns of patients with ATTR-CM in Taiwan, Hong Kong, and Malaysia. Therefore, a multicenter, noninterventional, disease registry study design was selected. The study aims to recruit patients diagnosed with ATTR-CM from approximately 17 sites in Taiwan, Hong Kong, and Malaysia. To be included in the study, patients will need to be adults (aged ≥18 years) at first ATTR-CM diagnosis or confirmed diagnosis of ATTR-CM after June 1, 2019. Reflected in the small number of global ATTR-CM studies, there is an absence of studies describing the populations of patients with ATTR-CM in Taiwan, Hong Kong, and Malaysia as such this study will ensure that the necessary data is available to improve the understanding of ATTR-CM [4]. The data collection was designed to align with routine clinical practice, following local standard practice guidelines.

ATTR is a variable disease, both phenotypically and geographically and TTR mutations appear to exist on an ethnic-specific spectrum [22-25]. In other studies, the most common TTR mutation is Thr60Ala in the UK and US patients, Val30Met in Japanese patients, Asp38Ala in South Korean patients, and Val30Met in Portuguese, Swedish, and Japanese patients while the Val122Ile mutation is endemic in the African-American population [26]. It is important not to rely solely on global data or data from other countries to inform the manifestation of ATTR-CM in Taiwan, Hong Kong, and Malaysia, particularly as Ala97aSer, the most common endemic mutation across these countries, which is less prevalent across the rest of the world, and as such has fewer reported cases and studies [27,28].

Across the global population as well as within individual nations, ATTR-CM has not received sufficient recognition, diagnosis, or treatment due to low public awareness and the absence of an effective therapeutic approach. However, even though there is a new understanding of the diagnosis, progression, and treatment of this disease worldwide [29], the prevalence and mortality rates based on real-world evidence (RWE) remain unknown in Asia [4]. This gap underscores the necessity for real-world data collection in Asia and this study is an initiative to fill in this knowledge void, starting with a clinical registry across Taiwan, Hong Kong, and Malaysia.

Establishing registries for rare diseases like ATTR-CM is fundamental to enhancing patient care pathways and ultimately improving disease outcomes [30,31]. Such registries are instrumental in generating RWE; they offer a systematic approach to monitor disease progression and assess the efficacy and safety of various treatment modalities [32]. The data compiled as per this protocol will enable a comprehensive understanding of ATTR-CM in the Asian context. An ATTR-CM registry for Asian countries is a critical step toward evaluating health care burden, clinical progression, health care strategies, and potential disparities. It will also facilitate a deeper analysis of treatment efficacy and safety, thereby improving the overall standard of care for patients with ATTR-CM [4].

As a multicenter, noninterventional, disease registry study aiming to collect real-world data on ATTR-CM, there are multiple strengths with this study design. Given the frequent undiagnosed instances of ATTR-CM in various clinical settings, this protocol is designed to ensure that the study sample accurately represents the target population through systematic patient assessment, nonrestrictive recruitment, and inclusive inclusion criteria. However, there are also some potential limitations inherent to the design of any multicountry and multicentric study. Center selection was based on each center’s readiness to participate and the availability of patients diagnosed with ATTR-CM. Consequently, while the protocol uses systematic patient assessment with broad, inclusive criteria, the study sample may not fully capture the national or regional prevalence or diagnosis rates of ATTR-CM. This targeted recruitment approach may introduce selection bias, potentially limiting the generalizability of the findings. Furthermore, variations in routine clinical care and adherence to standard practice guidelines across these multiple sites in different countries may affect the consistency, completeness, and types of data collected.

Despite these limitations, this study aims to make substantial contributions to the limited existing literature on ATTR-CM by documenting the natural history and treatment patterns of patients in Taiwan, Hong Kong, and Malaysia. It holds the potential to improve the detection and management of ATTR-CM in Asia, ultimately improving patient outcomes and increasing survival rates.

